## Abstract

**Background:** Deficits in neuromuscular control are widely reported after mild traumatic brain injury (mTBI). These deficits are speculated to contribute to the increased rate of musculoskeletal injuries after mTBI. However, a concrete mechanistic connection between post-mTBI deficits and musculoskeletal injuries has yet to be established. While impairments in some domains of balance control have been linked to musculoskeletal injuries, reactive balance control has received little attention in the mTBI literature, despite the inherent demand of balance recovery in athletics. Our central hypothesis is that the high rate of musculoskeletal injuries after mTBI is in part due to impaired reactive balance control necessary for balance recovery. The purpose of this study is to (1) characterize reactive postural responses to recover balance in athletes with recent mTBI compared to healthy control subjects, (2) determine the extent to which reactive postural responses remain impaired in athletes with recent mTBI who have been cleared to return to play, and (3) determine the relationship between reactive postural responses and acute lower extremity musculoskeletal injuries in a general sample of healthy collegiate athletes.

**Methods:** This two-phase study will take place at the University of Utah in coordination with the University of Utah Athletics Department. Phase 1 will evaluate student-athletes who have sustained mTBI and teammate-matched controls who meet all the inclusion criteria. The participants will be assessed at multiple time points along the return-to-play progress of the athlete with mTBI. The primary outcome will be measures of reactive postural response derived from wearable sensors during the Push and Release (P&R) test. In phase 2, student-athletes will undergo a baseline assessment of postural responses. Acute lower extremity musculoskeletal injuries for each participant will be prospectively tracked for 1 year from the date of first team activity. The primary outcomes will be the measures of reactive postural responses and the time from first team activity to lower extremity injury.

**Discussion:** Results from this study will further our understanding of changes in balance control, across all domains, after mTBI and identify the extent to which postural responses can be used to assess injury risk in collegiate athletes.

## Introduction

Standing balance problems are well documented in collegiate athletes after mild traumatic brain injury (mTBI) (Guskiewicz, 2011; Broglio et al., 2014). However, the Balance Error Scoring System (BESS), the most common clinical balance assessment for a suspected mTBI, only subjectively measures postural control in a variety of static conditions (Riemann and Guskiewicz, 2000). The BESS and other clinical tests, such as the standard Romberg test (Guskiewicz, 2011), struggle to detect subtle balance deficits that persist throughout an athlete's recovery from mTBI (Buckley et al., 2018) and therefore may be limited in their ability to determine return-to-play (RTP) readiness. Additionally, postural demands during athletic pursuits are not static. Recent studies suggest clinical testing of dynamic balance using the timed tandem gait test has clinical utility in mTBI management (Oldham et al., 2018). However, other aspects of balance control remain untested in mTBI management.

Balance control can be separated into three domains based on the goal of the task: (1) maintaining a posture (e.g., standing balance), (2) transitioning between postures with voluntary movement (e.g., gait, turning, gait initiation/termination, standing from a chair), or (3) restoring stability (e.g., recovering from a trip, slip, or push) (Pollock et al., 2000). Objective measures of standing balance from instrumented force platforms (DeBeaumont et al., 2011; Quatman-Yates et al., 2015; Fino et al., 2016b) and inertial sensors (King et al., 2014; Parrington et al., 2019) suggest maintenance of posture can remain impaired beyond the clinical RTP decision in athletes, and gait and turning abnormalities suggest postural control during transitions may also be affected for up to 1 year after mTBI (Fino et al., 2016a, 2018). Yet, there is limited knowledge of how mTBI affects the restoration of stability after loss of balance. There is evidence to suggest that mTBI history affects stability after dynamic movement in athletes (Lynall et al., 2020). However, no study has examined reactive stabilization following an unexpected external disturbance in athletes after mTBI. Considering athletes are frequently required to recover balance after an external perturbation or sudden destabilizing event, examining the effects of mTBI on restoring stability is important for a comprehensive understanding of the impact of mTBI in real-world and sporting environments.

Reactive postural responses rely on short-, medium-, and long-latency responses, resulting from interaction among spinal circuits, the brainstem, and the cerebral cortex. The short-latency response is likely spinally mediated and is too small to stabilize balance, whereas medium- and long-latency responses are mediated by the brainstem and cortex and stabilize balance via whole-body, synergistic muscle activations (Jacobs and Horak, 2007). During change in support responses in particular, a transcortical loop through the motor cortex is involved in initiation (Jacobs and Horak, 2007). Yet, the response to a perturbation is also dependent on the preperturbation central set, which is the neuromotor state resulting from changes in initial contexts such as changes in cognitive state or sensorimotor conditions (Jacobs and Horak, 2007). Prior to a loss of balance, cortical loops update the central set to prime postural responses (Jacobs and Horak, 2007; Mochizuki et al., 2008) in an anticipatory manner according to stored visual information about the surrounding environment (Maki et al., 2001; Zettel et al., 2005, 2008a,b). Because attentional resources may be required to maintain an appropriate central set, concurrent cognitive demands can limit this anticipatory preparation; attentional resources switch from the concurrent cognitive task to the balance-recovery task after the postural disturbance (Maki and McIlroy, 2007), and delayed set-switching can compromise the ensuing stepping response (Maki et al., 2001). Concurrent cognitive tasks also attenuate the N1 perturbation-evoked response within the medial prefrontal cortex (Quant et al., 2004) associated with task-switching (Rushworth et al., 2002). Persistent executive and attentional dysfunction (Howell et al., 2013b) and lasting structural and functional neuroimaging abnormalities within the frontal and prefrontal cortex (Chamard et al., 2016; Churchill et al., 2017a,b,c; Bigler, 2018), may limit the cognitive reserve (Stern, 2009) for completing simultaneous tasks after mTBI and could be responsible for impaired dual-task balance. Based on these previous findings, we posit that persistently slower set-switching reaction times and larger switch costs after mTBI (Mayr et al., 2014; Moore et al., 2014) may adversely affect balance recovery, particularly in highly dynamic sporting environments with changing motor and cognitive demands. While dual-task paradigms involving simultaneous static or dynamic balance and cognitive tasks elicit large balance deficits in individuals with mTBI (Howell et al., 2013a; Lee et al., 2013; Register-Mihalik et al., 2013; Fino et al., 2018), the influence of cognitive demands on the ability to restore stability remains unclear after mTBI.

Numerous research groups suspect that there is a link between impaired neuromuscular control and musculoskeletal injuries after mTBI. Notably, both of these aspects have solid grounding in the literature; deficits in neuromuscular control after mTBI are widely reported in the literature (Howell et al., 2018b; Wilkerson et al., 2018) and musculoskeletal injuries are around two times more likely after mTBI (Nordström et al., 2014; Lynall et al., 2015, 2017; Pietrosimone et al., 2015; Brooks et al., 2016; Cross et al., 2016; Gilbert et al., 2016; Herman et al., 2017; Fino et al., 2019; Reneker et al., 2019). Recently, dual-task gait impairment after mTBI has been linked to musculoskeletal injury risk (Howell et al., 2018a). Despite the overlap and apparent connection, a concrete connection between post-mTBI deficits and musculoskeletal injuries has yet to be established. Although absent from mTBI literature to date, imprecise responses following a loss of balance may contribute to the high rate of musculoskeletal injuries after mTBI. In healthy collegiate athletes, postural responses following the release of a sustained force at the trunk, with the lower body fixed, are highly associated with future injuries to the low back (Cholewicki et al., 2005) and knee (Zazulak et al., 2007). Disrupted perception–action coupling has been suggested as an alternative potential mechanism for post-mTBI musculoskeletal injury. This theory suggests that neurophysiological dysfunction stemming from mTBI dysregulates the perception–action coupling loop (Eagle et al., 2020); misestimating one's abilities (both the participant's physical abilities related to the environment and the participant's perception based on repeated action in the environment) may manifest in improper timing of movement or body position and increase behavioral risk after mTBI (Eagle et al., 2020). However, direct experimental evidence is lacking.

Two major challenges in establishing the connection between musculoskeletal injury risk and neuromuscular deficits are the lack of sensitivity of assessments and obtaining adequate sample size. Clinical tests often lack sensitivity and specificity, particularly to subtle motor deficits that may have practical implications. There is growing interest in using neuroimaging and serum biomarkers to examine changes in cerebrovascular reactivity (Churchill et al., 2020) and systemic inflammation (Di Battista et al., 2019) after mTBI, but a direct connection between mTBI and musculoskeletal injury risk remains unclear. In a recent study, several clinical tests including the standard assessment of concussion (SAC), BESS, Immediate Post-Concussion Assessment and Cognitive Training (ImPACT), clinical reaction time, and the King-Devick failed to predict musculoskeletal injury risk after mTBI (Buckley et al., 2020). As a consequence, more sophisticated tests and instrumentation are often used to determine post-mTBI neuromuscular deficits. These assessments, often conducted within biomechanical laboratories, are not feasible in clinical settings, a necessary requirement for adequate power and future clinical translation. Recent technological advances in wearable, inertial sensors may be capable of addressing these limitations by enabling objective and sensitive assessments in clinical settings (Horak et al., 2015; Nouredanesh and Tung, 2015; El-Gohary et al., 2017). For example, instrumenting the BESS with a single inertial sensor identified acute mTBI more accurately than the clinical error count (King et al., 2017; Parrington et al., 2018). Inertial sensors can identify subtle deficits in gait, distinguishing between healthy controls and individuals within 72 h of mTBI and up to 2 weeks postinjury (Howell et al., 2015). Recently, objective qualities of gait, quantified with inertial sensors, differed between athletes with mTBI who went on to sustain a future lower extremity musculoskeletal injury and those who did not (Oldham et al., 2020). Similarly, worsening dual task cost of walking speed throughout mTBI recovery was associated with risk of incurring a sport-related injury during the year following mTBI (Howell et al., 2018a). Because inertial sensors are portable and clinically feasible, they can be used to facilitate clinical testing on large numbers of collegiate athletes.

Similar to static balance and gait, clinical assessments of reactive postural responses in other populations rely on scoring guidelines based on visual observation, but wireless, wearable inertial sensors can improve the accuracy of these assessments. For example, inertial sensors can detect differences in reactive postural responses between disease states [healthy control, multiple sclerosis (Smith et al., 2016; El-Gohary et al., 2017), Parkinson disease (Smith et al., 2016)]. Wearable sensors also provide information about quality of movement using a variety of objective characteristics. However, no study has used inertial sensors to quantify reactive postural responses in clinical mTBI settings. Improved understanding of how mTBI impacts the quality of balance recovery is critical to determine the implications of persistent balance impairments after mTBI, such as increased injury risk, and to develop clinical rehabilitation strategies to optimize athletes' neuromuscular control prior to return to competitive activity.

Our central hypothesis is that the high rate of musculoskeletal injuries after mTBI is in part due to impaired postural responses and balance recovery. Therefore, the purpose of this study is to (1) characterize reactive postural responses in athletes with recent mTBI compared to healthy control subjects, (2) determine the extent to which postural responses remain impaired in athletes with recent mTBI who have been cleared to RTP, and (3) determine the relationship between postural responses and acute lower extremity musculoskeletal injuries in a general sample of healthy collegiate athletes. We hypothesize that (1a) athletes with recent mTBI will take longer to regain balance during assessments of reactive postural responses compared to control athletes; (1b) athletes with recent mTBI will have larger deficits, in postural responses when simultaneously performing a dual task, relative to single task; (2) athletes with recent mTBI will improve reactive postural responses but will still demonstrate deficits compared to control subjects at all time points; (3a) that impaired postural responses at a baseline assessment will be associated with a faster time to acute musculoskeletal injury in healthy collegiate athletes; and (3b) objective measures of reactive postural responses will be better predictors of musculoskeletal injuries compared to clinical measures.

## Methods

This study has two phases that will run concurrently. Phase 1 includes the first two aims: (1) to evaluate acute differences in postural responses after mTBI and (2) to evaluate persistent mTBI-related deficits in postural responses after RTP. Phase 2 contains the third aim: to characterize associations between baseline variations in postural responses and prospective lower extremity injuries in healthy athletes.

### Phase 1: Characterization of Postural Responses After mTBI and Persistent mTBI-Related Deficits

#### Participants

For phase 1, 80 subjects will be recruited (40 athletes who experienced recent mTBI and 40 healthy teammate controls, matched on position and practice exposure). Sports medicine fellowship–trained team physicians with at least 10 years of training and clinical experience will diagnose mTBI based on history and physical examination, which is currently the gold standard. All subjects will be between the ages of 18 and 30 years and tested on site in the Athletic Training Clinics at the University of Utah. Informed written consent will be obtained from all participants.

#### Inclusion and Exclusion Criteria

For phase 1, inclusion criteria for mTBI recruitment are (1) age 18 to 30 years, (2) current participant in NCAA Division I athletics, and (3) mTBI within last 10 days (subjects must be assessed before beginning RTP protocol, even if acute time point is missed). Exclusion criteria for mTBI subjects are (1) previous history of vestibular or somatosensory pathology, (2) history of major injury to either leg requiring surgery within the last 2 years, and (3) body mass index (BMI) >40 kg/m^2^. Inclusion criteria for matched controls are (1) age 18–30 years, (2) current participant in NCAA Division I athletics. Exclusion criteria for healthy control subjects are (1) previous history of vestibular or somatosensory pathology, (2) recent mTBI (<1 year), (3) history of major injury to either leg requiring surgery within the last 2 years, and (4) BMI >40 kg/m^2^.

#### Assessment Procedures

For phase 1, athletes will be assessed at four time points: (1) within 48 h of mTBI (acute), (2) within 24 h of starting RTP protocol (PreRTP), (3) within 24 h of being medically cleared for RTP (PostRTP), and (4) ~6 months after injury (6Month). Assessments will take ~15 min and will be administered at the end of current Pac-12 CARE Affiliated Project (CAP) testing (Broglio et al., 2017). CAP testing is a tablet-based battery of measures that examine personal and family health history, neurocognitive assessments, neurological status, postural stability, symptoms, and oculomotor/oculovestibular function. Tests included in CAP testing are the Sport Concussion Assessment Tool, Fifth Edition; BESS; Brief Symptom Inventory 18; SAC; ImPACT; and EYESYNC (SyncThink, Palo Alto, CA) measures (Maruta et al., 2018). Assessments of matched control subjects will be tested within 24 h of the testing session of the athlete with mTBI. Return to play will follow guidelines set forth by the University of Utah Concussion Management Plan. Athletes will progress to RTP when, under the guidance of the physician and athletic trainer, the assessment battery including symptom assessment, ImPACT, and BESS has normalized. In the current study, athletes will be cleared to start RTP by only a limited number of team physicians.

Within 48 h from the time of the mTBI, informed written consent will be obtained from the athlete with mTBI and the matched control teammate. A total of 40 athletes with mTBI and 40 matched control athletes will complete assessments at four time points (Acute, PreRTP, PostRTP, 6Month). Each assessment will include questionnaires, clinical tests of function, and instrumented assessments of reactive postural responses (Table 1).

**Table 1 T1:** Questionnaires, surveys, and tests utilized in the present study with description of subject group (mTBI, control, both) and time point (Acute, PreRTP, PostRTP, 6Month, all).

**Validated Questionnaires**	**Purpose**	**Subject group**	**Time point**
Multidimensional fatigue inventory	Multiple domains of fatigue	Both	All
Pittsburgh sleep quality index	Sleep quality and disturbances and daytime dysfunction	Both	All
Injury-psychological readiness to return to sport scale	Confidence to return to play	mTBI	All
Return to sport after serious injury questionnaire	Motivation underlying return to play	mTBI	6 month
**Patient self-report**	**Purpose**	**Subject group**	**Time point**
Questions adapted from the OSU TBI-ID	Concussion history	Both	Acute, 6 month
Questions regarding recent (<2 years) lower extremity musculoskeletal injury and surgery history	Lower extremity injury and surgery history	Both	All
Questions regarding return-to-learn progress	Return-to-learn	mTBI	All
Questions regarding medication use postconcussion	Medication use	mTBI	All
**Test**	**Purpose**	**Subject group**	**Time point**
Clinical reaction time (drop stick test)	Clinical reaction time	Both	All
Instrumented balance error scoring system	Static balance	Both	All
Push and release test	Reactive postural response	Both	All

##### Questionnaires

At every time point, the athlete with mTBI will complete the following questionnaires: Multidimensional Fatigue Inventory (MFI), Pittsburgh Sleep Quality Index (PSQI), Injury-Psychological Readiness to Return to Sport (I-PRRS) scale. The MFI is a 20-item questionnaire designed to measure the following domains of fatigue: general fatigue, physical fatigue, mental fatigue, motivation, and activity (Smets et al., 1995). The PSQI is a 19-item questionnaire designed to assess sleep quality, sleep disturbances, and daytime dysfunction. In the present study we will exclude the five questions rated by the bed-partner or roommate (Buysse et al., 1989). The I-PRRS scale is a sport psychometric test to assess injured athletes' confidence and psychological readiness to return to play (Glazer, 2009). Athletes are asked to rate their confidence on a scale of 0 to 100 on six items related to competing in their sport. To determine motivation underlying return to sport, at the 6Month time point, the athlete with mTBI will also complete the 21-item Return to Sport after Serious Injury Questionnaire (Podlog and Eklund, 2005). Information regarding return-to-learn experience and medication use after mTBI will also be obtained. The matched control athlete will complete the MFI and PSQI at every time point.

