#### Assessment Procedures

Phase 2 assessments will be included as part of preseason physical baseline testing. Acute lower extremity musculoskeletal injuries for each athlete in phase 2 will be prospectively tracked for 1 year from the date of first team activity.

The phase 2 assessment will be identical to the phase 1 matched control athlete assessment. Additionally, mTBI history will be recorded using the Ohio State Traumatic Brain Injury Identification Method (OSU TBI-ID). While the OSU TBI-ID is not made specifically for mTBI, it is well validated (Corrigan and Bogner, 2007; Bogner and Corrigan, 2009) and recommended by the National Institute of Neurological Disorders and Stroke as a Common Data Element for mTBI studies. Lower extremity injury history, including the date of injury, location, type of injury (e.g., sprain, fracture), cause, time lost from sport, and relation of each injury to the athlete's primary sport, will be recorded.

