#### Statistical Analysis

Time from first team activity to first musculoskeletal injury will be summarized using Kaplan–Meier methods. Cox proportional hazards models will be constructed to determine if time to stabilization during postural responses is associated with faster times to injury in the general collegiate athlete population (hypothesis 3a). Similar models will be performed for each secondary outcome. Models will first be unadjusted and then potentially adjusted for age, gender, sport, history of a recent musculoskeletal injury, and history of mTBI before enrollment. The number of variables that we will adjust for will depend on the number of musculoskeletal injuries observed. The inclusion of sport as a covariate will account for variation in the biomechanical demands, exposures, and schedules across different sports. To determine if time to stabilization is a better predictor of future injury than clinical score, similar models will be constructed for the P&R clinical score, and we will assess each model's predictive ability using c-statistics (hypothesis 3b). Models with the highest c-statistic value will indicate the outcome most predictive of time to injury.

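### Phase 2 measures fatigue and sleep at the same baseline as the push and release test, but the named Cox covariates include neither, so the planned models cannot show whether a stabilization–injury association reflects them

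*Protocol article*

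**What the plan says.** All references are to the protocol article.

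- **Phase 1, Questionnaires:** "The matched control athlete will complete the MFI and PSQI at every time point". The MFI covers several domains of fatigue. The PSQI covers sleep quality, sleep disturbance and daytime dysfunction.
- **Phase 1, Assessment Procedures:** "Each assessment will include questionnaires, clinical tests of function, and instrumented assessments of reactive postural responses". Table 1 lists the MFI, the PSQI and the push and release test for both groups at all time points.
- **Phase 2, Assessment Procedures:** "The phase 2 assessment will be identical to the phase 1 matched control athlete assessment", and "Phase 2 assessments will be included as part of preseason physical baseline testing". The MFI and PSQI are therefore part of the same preseason baseline as the push and release test.
- **Phase 2, Statistical Analysis:** "Cox proportional hazards models will be constructed to determine if time to stabilization during postural responses is associated with faster times to injury". On adjustment: "Models will first be unadjusted and then potentially adjusted for age, gender, sport, history of a recent musculoskeletal injury, and history of mTBI before enrollment". And: "The number of variables that we will adjust for will depend on the number of musculoskeletal injuries observed".

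Neither statistical analysis section, for phase 1 or phase 2, gives the MFI or PSQI a role.

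**The concern.** Hypothesis 3a is worded as an association, but the article gives it a causal job. The Introduction's central hypothesis attributes part of the injury rate after mTBI to impaired postural responses. The Discussion makes that contribution the study's primary goal and carries the phase 2 association over to athletes with mTBI.

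A tired or poorly rested athlete might stabilize more slowly on the test day and might also be injured sooner for other reasons. The hazard ratio for time to stabilization would then partly reflect fatigue or sleep. The Introduction gives some support for the first link: it says the response to a perturbation depends on a preparatory state that varies with cognitive state and may need attention to maintain. The second link, from fatigue or sleep to injury, is not addressed in the article.

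At stake is how a positive result for hypothesis 3a is interpreted. The data that could test this alternative explanation are collected but are not on the list of candidate covariates.

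**Working it through.** **1. The plan's own figure.** Inputs from phase 2, Sample Size Justification: N = 200, event rate 22%, SD 1 s, HR 1.53 per 1 s, significance level 0.05 (taken as two-sided).

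- Expected events: 200 × 0.22 = 44.
- Events needed = (z₀.₉₇₅ + z₀.₈₀)² / (SD² × (ln HR)²) = 7.849 / 0.4253² = 43.4, so N = 43.4 / 0.22 = 197.3, rounded up to 198.
- Power with 44 events = Φ(√44 × 0.4253 − 1.96) = 80.5%.
- Minimum detectable HR = exp(2.802 / √44) = 1.526.

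The stated 80% and 1.53 reproduce. The calculation is for an unadjusted model and is not in question.

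**2. Possible size of the bias.** The documents give no correlation between fatigue or sleep and stabilization time, and no injury hazard ratio for either, so every r and h below is an assumption. Let r be the correlation of a fatigue score with stabilization time and h the injury HR per SD of that score, with no effect of stabilization time itself. Approximately:

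- spurious log HR per SD: b = r × ln h
- standard error: 1/√44
- two-sided rejection rate: Φ(√44·b − 1.96) + Φ(−√44·b − 1.96)

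| r | h | b | spurious HR | √44·b | rejection, formula | rejection, simulation |
|---|---|---|---|---|---|---|
| 0.1 | 1.25 | 0.022 | 1.02 | 0.15 | 5.3% | 5% |
| 0.2 | 1.3 | 0.052 | 1.05 | 0.35 | 6.4% | 7.2% |
| 0.3 | 1.3 | 0.079 | 1.08 | 0.52 | 8.2% | 9.0% |
| 0.3 | 1.5 | 0.122 | 1.13 | 0.81 | 12.7% | 12% |
| 0.4 | 1.5 | 0.162 | 1.18 | 1.08 | 19.0% | 18.0% |

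The simulations used 200 athletes, a one-year event rate of about 22% and exponential event times. An extreme case (r 0.5, h 2.0) gives a spurious HR of 1.41 and 63% by formula, or 1.39 and 57% by simulation. In the three scenarios also simulated with the fatigue score in the model (r 0.1, h 1.25; r 0.3, h 1.5; r 0.5, h 2.0), the HR returned to 0.99–1.00 and rejection to 4–6%. That assumes the score measures fatigue without error.

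**3. Cost of the added model.** If the added scores explain a share R² of the variance of stabilization time (again assumed), effective events are 44 × (1 − R²).

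| R² | effective events | power at HR 1.53 | minimum detectable HR |
|---|---|---|---|
| 0.04 | 42.2 | 78.9% | 1.54 |
| 0.09 | 40.0 | 76.8% | 1.56 |
| 0.16 | 37.0 | 73.4% | 1.59 |

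Stabilization time plus one MFI score and one PSQI score is three parameters: 44 / 3 = 14.7 events each.

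**The case against.** **The confounding is not documented.** The article does not show that fatigue or sleep slows stabilization or that either raises injury risk. At the weak end of the range the bias is trivial. If fatigue affected injury only through the postural response, there would be no confounding. All of this stands. A reader might infer that the phase 2 hazard ratio is biased upward; the documents support only that it could be.

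**Phase 2 athletes are not free of mTBI effects.** A reader might infer that fatigue and sleep must be common causes here because phase 2 athletes have no index mTBI. The phase 2 exclusion criteria do not bar a recent mTBI, whereas phase 1 controls are excluded for one within a year. The Discussion also describes the phase 2 population as irrespective of mTBI. In some athletes an earlier mTBI may lie behind both the questionnaire scores and the slow response. This stands, and it limits how any attenuation can be read.

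**An article condenses the plan.** It states no analysis for several other ancillary measures, and the covariates are only potential ones. This stands in part: not using every collected variable is neither a contradiction nor an error. But the article names its candidates and leaves open how many will be used, and neither score is among those named.

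**Events are scarce.** With about 44 events, preferring sport, injury history and mTBI history is defensible. A three-parameter model that omits them is a different partial adjustment, not a better one. This stands, and it is why the extra model should sit beside the planned ones and not replace them.

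**A gate would be wrong.** A reader might infer that an association should be claimed only if it survives adjustment. An attenuated association is still an association, and hypothesis 3a is worded as one. Such a rule would also need a threshold that nothing in the documents supplies.

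**Conclusion.** The point holds as a cheap improvement, not as an error in the plan. Phase 2 collects MFI and PSQI scores in the same baseline assessment as the exposure, and the named Cox covariates omit both. The models as described therefore cannot separate a postural-response association from one that reflects fatigue or poor sleep.

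The size is unknown. Under the assumed inputs in the first table, the false-positive rate runs from close to nominal (about 5%) to 18–19%, with spurious hazard ratios from 1.02 to about 1.18. The documents do not say where in that range, or outside it, the study lies.

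The point concerns the causal reading of hypothesis 3a only. The c-statistic comparison in hypothesis 3b is predictive and does not need confounder control.

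**What to change.** Keep the planned unadjusted and adjusted models for hypothesis 3a. Prespecify one sensitivity model that adds a single MFI score (for example general fatigue, chosen in advance) and the PSQI global score to time to stabilization. If the number of injuries allows, add the same two scores to the planned adjusted model as well. Do not enter all the MFI domains.

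Report the hazard ratio and interval from this model beside the planned ones, with no pass/fail rule. If the estimate is attenuated, temper the causal interpretation and say that earlier mTBI may contribute to the scores in some athletes.

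The cost is two more parameters on about 44 events, hence a wider interval in that model: power at HR 1.53 of about 79% to 73% if the scores explain 4% to 16% of the variance of stabilization time. No new data are needed, and the planned analyses keep their stated power.
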